### Data management and adverse event reporting

After initial telephone screening, all eligible participants will be given a unique code to be used for all forms and data collection to de-identify participants. Consent forms and allocation of identification numbers will be stored in a password-protected format on a secure Deakin University server. Coded data collection forms will be stored securely at Deakin University. For the duration of the study, data collected will be available only to participating researchers.

After the completion of the trial, dissemination of research results will only consist of aggregated data; individual participants will not be identified. Findings from this project will be released to relevant agencies and health care professionals that could potentially benefit from these findings. The study results will also be presented at national and international conferences and will appear in our annual reports and newsletters. Should participants wish to have access to their corresponding results, a brief report via email or post will be provided and copies of published articles will be sent via email or post at the end of the study. Information on paper copy, computer or CD will be stored for 15 years from the date of publication. After a period of 15 years from the date of any publication of the results from the study, paper copies of individual responses will be disposed of.

If an adverse event occurs, then the adverse event reporting form will be completed. The participant will be advised to contact his/her medical practitioner where necessary.

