**Methods/design:**

Forty participants, 25–45 years old with chronic (>3 months), non-specific low back pain will be recruited. Participants will be randomised to receive either motor control and manual therapy (*n* = 20) or general strength and conditioning (*n* = 20) exercise treatments for 6 months. The motor control/manual therapy group will receive twelve 30-min sessions, ten in the first 3 months (one or two per week) and two in the last 3 months. The general exercise group will attend two 1-hour sessions weekly for 3 months, and one or two a week for the following 3 months. Primary outcome measures are average lumbar spine intervertebral disc T2 relaxation time and changes in thickness of the transversus abdominis muscle on a leg lift using magnetic resonance imaging (MRI). Secondary outcomes include muscle size and fat content, vertebral body fat content, intervertebral disc morphology and water diffusion measured by MRI, body composition using dual energy X-ray absorptiometry, physical function through functional tests, changes in corticospinal excitability and cortical motor representation of the spinal muscles using transcranial magnetic stimulation and self-reported measure of pain symptoms, health and disability. Outcome measures will be conducted at baseline, at the 3-month follow-up and at 6 months at the end of intervention. Pain, depressive symptomology and emotions will be captured fortnightly by questionnaires.

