### Study interventions

#### Motor control and manual therapy (MCMT)

Participants randomised to the MCMT group will receive twelve 30-min one-on-one physiotherapy sessions, consistent with previous protocols in chronic low back pain care [57, 58]. In the first 3 months ten sessions (one to two sessions a week) will be delivered with two sessions in the final 3 months. Treatment will take place at Advance HealthCare in Boronia by qualified physiotherapists, and will include a motor control exercise program in conjunction with the application of manual therapy based on the Specific Treatment of Problems of the Spine (STOPS) protocol [58]. Graded functional exercises will be implemented, targeting the local stabilising muscles transversus abdominis, multifidus and the pelvic floor muscles [59]. Progression of exercises will be on a pain-contingent basis. The program aims to restore optimal motor control during daily activities [59, 60]. Along with motor control exercises, participants will be guided in modifying maladaptive kinematics with postural correction [60].

Manual therapy treatment will be included at the discretion of the treating physiotherapists. Treatment will be in accordance with key principles for spinal manual therapy [61] and will include posterior-anterior and transverse mobilisation using rotation and soft tissue techniques of the lumbar and pelvic region. Basic cognitive-behavioural education will be utilised as required to assist participants to overcome any distress that may account in part for their altered motor control (such as inability to relax the abdominal wall, concerns about the safety of exercising). Attendance at treatments will be recorded and reported at the 3-and 6-months follow-up. A home-based exercise program will also be arranged for participants to complete between sessions, which will include motor control, postural control and pelvic floor exercises taught at each session, before gradually introducing the motor control skills into everyday activities.

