#### General strength and conditioning (GSC)

Participants will complete a 6-month GSC training program, including gym-based supervised sessions and independent home-based exercises. An Accredited Exercise Physiologist (AEP) or Masters of Clinical Exercise Physiology students (supervised by an AEP) will administer the gym-based training in the Clinical Exercise Learning Centre (CELC), Deakin University, Burwood, Victoria or the Burwood YMCA at Deakin University. Participants will attend two 1-hour training sessions in weeks 1–12, and one to two training sessions per week in weeks 12–26. Sessions will consist of 20 min of aerobic conditioning, beginning at an intensity of 65–70% maximum heart rate (HR_max_) in the first 2 weeks and increasing to 65–85% HR_max_. This will be followed by progressive resistance training and proprioceptive exercises. Each session in the resistance program consists of five exercises from a selection of seven core exercises grouped according to an action: push, pull, trunk extension, trunk flexion and lift. The program follows training principles of undulating periodisation, varying loads, reps, sets and time under tension as shown in Table 1, Resistance training program overview. Progression will be determined with a time-contingent rather than pain-contingent manner, in line with previous studies on functional movement goals in perceived painful activity [62, 63]. Participants will receive pain education during the training sessions as required.

**Table 1 Tab1:** Resistance training program overview

Week	Goal	Intensity	Frequency	Routine	Time under tension	Progression
1–4	Familiarisation, motor control and local muscular endurance	12–15 reps performed at 2 reps below volitional fatigue × 2 sets, 1 min rest between sets	2/wk	Full body	2 s concentric, 2 s eccentric	Once 2 sets of 15 reps at 2 consecutive training sessions are completed, resistance is increased
5–10	Muscular strength	6–10 reps performed at 2 reps below volitional fatigue × 2–3 sets, 2 min rest between sets	2/wk	Full body	2 s concentric, 2 s eccentric	Once 2 sets of 10 reps at 2 consecutive training sessions are completed, workload increases to 3 sets. Then progression made through increased resistance
11	Light week	10 reps at 80% of resistance used in the previous week × 3 sets, 2 min rest between sets	2/wk	Full body	2 s concentric, 2 s eccentric	None

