## Discussion

It is well accepted that exercise is effective for reducing pain in those suffering chronic low back pain. Furthermore, reviews of various exercise approaches have revealed little differences in the impact on reducing pain between common exercise interventions including specific spinal exercises or general conditioning [87, 88]. However, the literature on this subject tends to solely focus on the effects of exercise on subjective pain levels. Additional deficits evident in low back pain have little data on the effects that certain exercise protocols have, which may contribute to successful treatment and management of chronic low back pain. This study aims to investigate and compare two treatment approaches for chronic low back pain that represent two distinct loading strategies. This trial will be one of the first to extensively examine the impact of different treatment approaches on multiple outcome domains and side effects in people with chronic low back pain. Although some outcome measurements used in this study are not easily replicable in clinical practice, the results of this study will help us understand the effect that different exercises have on various contributors to chronic low back pain, not just the pain itself. They will also help us determine if particular exercises are more favourable over general activity and movement. This study promises to support clinical practice by providing outcome-based evidence on the effectiveness of different exercises, and to help guide treatment decisions and exercise plans for patients with chronic low back pain.

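### Adverse events are recorded by an event-triggered form with no common enquiry, while supervised contact differs about 3-4 fold between arms, so the announced look at side effects is at risk of ascertainment bias

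*Protocol article*

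**What the plan says.** **Recording rule.** Under Data management and adverse event reporting: "If an adverse event occurs, then the adverse event reporting form will be completed". The same paragraph adds that participants are referred to their own doctor where needed. It does not say who asks about events, when, or with what question.

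**Purpose.** The Discussion presents the trial as one of the first "to extensively examine the impact of different treatment approaches on multiple outcome domains and side effects". Side effects are not a listed primary or secondary outcome.

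**Contact in MCMT.** "Participants randomised to the MCMT group will receive twelve 30-min one-on-one physiotherapy sessions", split as follows: "In the first 3 months ten sessions (one to two sessions a week) will be delivered with two sessions in the final 3 months".

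**Contact in GSC.** The intervention section gives "two 1-hour training sessions in weeks 1–12, and one to two training sessions per week in weeks 12–26". The Abstract makes the weekly frequency explicit: "The general exercise group will attend two 1-hour sessions weekly for 3 months, and one or two a week for the following 3 months".

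**Session records.** GSC staff log attendance, exercises, perceived exertion and duration, and give a reason for each missed session. For MCMT the stated record is attendance. Table 2 has one form that therapists complete at every session, the adherence scale (SIRAS).

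**Contact shared by both arms.** Assessments take place at baseline, 3 and 6 months. Pain, depressive symptoms and affect are collected fortnightly online. No instrument in Table 2 is described as an adverse-event enquiry.

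**The concern.** When a form is completed because an event has occurred, someone must first learn of the event. The natural occasion is a supervised session, and the arms differ widely in how many they have. They are also seen by different staff at different sites: physiotherapists at an outside clinic for MCMT, exercise physiologists or supervised students at the university for GSC. If the true event rates were equal, the arm seen more often would tend to have more forms.

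Two things are at stake. A tabulation of side effects by arm could make GSC look less safe than it is relative to MCMT, in a trial meant to guide treatment choice. And events in MCMT during months 4-6, when participants mostly exercise at home, have fewer occasions to be noticed.

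**Working it through.** **1. Sessions per arm**

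- MCMT: 10 + 2 = 12, which reproduces the stated total of twelve.
- GSC, months 1-3: 2 per week × 12 weeks = 24.
- GSC, months 4-6, taken as 14 weeks: 14 × 1 = 14 to 14 × 2 = 28.
- GSC total: 24 + 14 = 38 to 24 + 28 = 52. The document states no GSC total to compare with this.

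**2. Ratios, GSC to MCMT**

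| Period | GSC | MCMT | Ratio |
|---|---|---|---|
| Months 1-3 | 24 | 10 | 2.4 |
| Months 4-6 | 14-28 | 2 | 7-14 |
| Whole trial | 38-52 | 12 | 3.2-4.3 |
| Supervised hours | 38-52 | 12 × 0.5 = 6 | 6.3-8.7 |

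The hours assume that GSC sessions stay at one hour throughout.

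**3. Sensitivity to the week count.** The GSC text counts week 12 in both periods, and Table 1 ends at week 25.

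- Table 1: 11 weeks × 2 = 22, plus 14-28, gives 36-50 sessions, a ratio of 3.0-4.2.
- Fifteen later weeks (12 to 26 inclusive): 24 + 15 = 39 to 24 + 30 = 54, a ratio of 3.3-4.5.

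Across these readings the overall ratio is 3.0-4.5.

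**4. Allowing for contact shared by both arms**

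- Assume four common visits after randomisation (one test day and one MRI at each of 3 and 6 months): (38 + 4)/(12 + 4) = 2.6 to (52 + 4)/16 = 3.5.
- Count about 13 fortnightly questionnaires (26 weeks / 2) as contacts too: (38 + 17)/(12 + 17) = 1.9 to (52 + 17)/29 = 2.4.

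The second figure is generous to the plan, because those questionnaires contain no adverse-event item and no stated rule links an answer to the form.

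**5. What this could do to recorded events.** The document gives no event rate and no chance of detection, so this step is an illustration on assumed values. Suppose the true rate is the same in both arms, and each session has an independent probability p of bringing an event to notice. The true rate cancels, and the ratio of recorded rates is

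[1 − (1 − p)^n] / [1 − (1 − p)^12], with n = 38 to 52.

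| Assumed p | Recorded GSC/MCMT ratio |
|---|---|
| 2% | 2.5-3.0 |
| 5% | 1.9-2.0 |
| 10% | 1.4 |

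Shared contacts are left out, and including them would pull these ratios towards 1. The direction is the same at every value; the size depends on p, which is unknown.

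**The case against.** **It rests on silence in a condensed article.** The full protocol and the adverse event form are not shown and may set a structured enquiry. If they do, with equal timing in both arms, the concern falls away. That event detection is purely passive is something a reader might infer; the article does not say so. But the point does not rest on a missing detail alone. The article states an event-triggered rule, an itemised questionnaire schedule without an adverse-event item, and unequal contact. Following these as written gives the arms unequal opportunity for detection.

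**Much contact is equal.** This stands in part. Both arms get the fortnightly questionnaires, and at 3 and 6 months both complete the sciatica index, medication usage, the disability questionnaire and the global rating of change. These would pick up back-pain flares and leg symptoms on the same schedule. It would therefore be wrong to infer that MCMT events have almost no route to the form in months 4-6. The instruments do not ask about other injuries, reactions to treatment or care sought.

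**No comparison of harms is specified.** Correct. The intention appears only in the Discussion, and the Statistical analysis section covers continuous variables. No specified test is shown to be biased; what is at risk is whatever account of side effects by treatment is eventually given.

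**More sessions mean more exposure.** Also correct. GSC delivers far more supervised exercise, so some excess could be a true effect. Unequal detection makes that harder to tell.

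**Conclusion.** The concern holds as a risk. Supervised contact differs about 3-4 fold overall and 7-14 fold in months 4-6, the stated recording rule has no enquiry common to both arms, and missed-session reasons are stated only for GSC. An examination of side effects by treatment is therefore open to ascertainment bias, probably towards more recorded events in GSC. This rests on reading the GSC schedule as sessions per week, as the Abstract does, and on the article being complete about how events are elicited.

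Two stronger readings are tempting and are not supported:

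- *That the comparison is biased and GSC will look more harmful.* Without an event rate or a detection probability, only a risk and a likely direction can be stated.
- *That equal rates would show as about a threefold GSC excess.* This follows only if an event in months 4-6 is captured solely when a visit comes within two weeks: MCMT then covers 2 × 2 = 4 of 14 weeks (29%), against about all weeks in GSC. Counting the common 6-month assessment as a third MCMT contact gives 6 of 14 weeks (43%) and a ratio of 14/6 = 2.3. If participants recall earlier events at that visit, the arms come closer still. The figure is set by its assumption.

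The point merits a change to the plan, because events never asked about cannot be reliably recovered at analysis.

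**What to change.** Add one identically worded adverse-event question to the fortnightly online questionnaire that both arms already receive, and repeat it at the 3- and 6-month assessments. It could cover any new or worsened symptom, care sought, and a session or activity missed because of it. State that any between-arm comparison of harms uses these solicited reports, and list spontaneously noted events separately by arm. Report the number of sessions attended alongside, so that readers can weigh differences in exposure.

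If the full protocol already contains an equal structured enquiry, a sentence saying so would be enough.

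The cost is one extra item in an existing questionnaire, an ethics notification and slightly more form handling. Recruitment was still under way when the article was submitted, so participants already enrolled would have solicited data only from the date of the change. That date should be reported, and person-time before and after it kept apart.

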### Statistical analysis

Mixed effects models with an intention-to-treat approach will be performed for all continuous variables to assess the interaction effect of the intervention over time (group × time). All statistical analyses will adopt a significance level of 0.05.

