### Sample size

Prior data on the impact of interventional exercise on the intervertebral disc do not exist. Recent cross-sectional work on habitual (minimum 5-year history) runners and sedentary individuals showed a 9–11% difference in lumbar IVD T2-time between these collectives [14]. For this first interventional study on exercise and IVD adaptation, we targeted a 0.5% change in lumbar IVD T2-time as a minimum detectable effect size. This compares to a 0.2–0.3% loss of lumbar IVD T2-time per 1 year with normal aging above the age of 30 [54]. Data from the research group ([name] et al., unpublished observations) show a mean (SD) lumbar IVD T2-time of 100.6 (12.4) with a correlation of 0.982 (coefficient of variation (CV): 1.7%) between repeated measures. To detect a 0.5% difference, or an effect size of 0.0406, on a group*time interaction in the change in lumbar IVD T2-time with two study arms and three measurement time-points, and assuming an alpha of 0.05 and a power of 0.8, a sample size of 36 would be required. Assuming 10% dropouts, this implies a total pool of 40 participants would need to be included in the study. G*Power (version 3.1.2) [55] was used for these calculations.

In reviewing the literature, we were not able to identify data on the reliability of measurement of contraction of the transversus abdominis muscle on MRI (Fig. 3). The current study should be considered a pilot study for the impact of the motor control intervention for contraction of the transversus abdominis muscle on MRI.

For the secondary outcome of muscle size, data from our previous work of average lumbar multifidus cross-sectional area showed a correlation of 0.948 between repeated measures with a mean (SD) of 559 (72) mm^2^ [56]. With a total sample size of 36 participants, an effect size of 0.89% or 4.97 mm^2^ between groups (group*time interaction) should be detectable.

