### Randomisation

Offsite randomisation procedures will ensure random and concealed allocation of participants. A researcher at La Trobe University who will have no contact with volunteers will randomise participants to either motor control and manual therapy (MCMT) or general strength and conditioning (GSC). A randomisation schedule (utilising block randomisation with random block lengths and stratification for gender) will be prepared in advance using a web-based randomisation program. Concealed allocation in accordance with the randomisation schedule will then be implemented by the researcher upon receipt of the name, gender and date of birth of a consenting participant to be enrolled into the trial.

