### Outcome measures

Outcome measures will be obtained from participants at baseline and at 3 and 6 months. Trained research staff will adhere to the standardised procedures for all data collection to ensure consistency in equipment used in each test and documentation and storage of data collected.

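### As written, the group-by-time test makes the treatment effect a difference in change from baseline; baseline adjustment is more efficient for outcomes with modest repeat correlation

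*Protocol article*

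**What the plan says.** The Statistical analysis section of the protocol article has two sentences. The first reads "Mixed effects models with an intention-to-treat approach will be performed for all continuous variables to assess the interaction effect of the intervention over time". The second reads "All statistical analyses will adopt a significance level of 0.05". Neither lists fixed effects or covariates.

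Two other sections show what time means in that interaction. Under Outcome measures: "Outcome measures will be obtained from participants at baseline and at 3 and 6 months". Under Sample size, the powered test is "on a group*time interaction in the change in lumbar IVD T2-time with two study arms and three measurement time-points". With measurements at 0, 3 and 6 months, the three time-points can only be baseline and the two follow-ups.

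The Randomisation section specifies "block randomisation with random block lengths and stratification for gender". The article does not say whether gender enters the analysis model, or whether the arms' baseline means are constrained to be equal.

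**The concern.** When baseline is one of the responses and each arm has its own baseline mean, the group-by-time terms are differences between arms in change from baseline. Randomisation guarantees equal baseline means in expectation. Such a model nevertheless estimates a baseline difference between arms and subtracts all of it from the follow-up difference. Regression on baseline subtracts only the share that baseline predicts.

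The lower the correlation between baseline and follow-up, the more noise the full subtraction adds. The same model is to be used for every continuous outcome. These include the second primary outcome, the change in transversus abdominis thickness on a leg lift, as well as pain, questionnaire and function measures. With 40 participants there is little precision to spare.

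**Working it through.** **Inputs.** From Sample size: T2-time "show a mean (SD) lumbar IVD T2-time of 100.6 (12.4) with a correlation of 0.982"; multifidus area, SD 72 and r = 0.948; 36 evaluable participants (18 per arm) out of 40 recruited. The same section says that no reliability data were found for transversus abdominis contraction. No correlation is given for pain, questionnaires or function. For all of these I assume r between 0.3 and 0.8.

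**The plan's own figure.** The article states "To detect a 0.5% difference, or an effect size of 0.0406" and "assuming an alpha of 0.05 and a power of 0.8, a sample size of 36 would be required". In the repeated-measures interaction F test with f = 0.0406, two arms, three time-points and r = 0.982:

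- Noncentrality = f² × N × 3 / (1 − r) = 0.0406² × 36 × 3 / 0.018 = 9.89.
- Degrees of freedom are 2 and 68, and power is 0.792.
- Dropout: 36 / 0.9 = 40.

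This agrees with the stated 36 to rounding (an even N first reaches 0.80 at 38) and confirms that baseline counts as one of three responses. Whether 0.0406, which is 0.503/12.4, should be entered as f is a separate question and does not affect this point.

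**Variance of the effect at one follow-up visit**, per participant, with equal variances σ² at each visit:

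- Difference in change: 2σ²(1 − r).
- Baseline-adjusted: σ²(1 − r²).
- Ratio: (1 − r²) / [2(1 − r)] = (1 + r)/2.

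| Outcome | r | Ratio | Participants giving the precision of 36 |
|---|---|---|---|
| T2-time | 0.982 (stated) | 0.991 | 35.7 |
| Multifidus area | 0.948 (stated) | 0.974 | 35.1 |
| No correlation given | 0.8 (assumed) | 0.90 | 32.4 |
| | 0.7 (assumed) | 0.85 | 30.6 |
| | 0.5 (assumed) | 0.75 | 27.0 |
| | 0.3 (assumed) | 0.65 | 23.4 |

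For T2-time at 18 per arm, the standard error falls from 12.4 × √(2 × 0.018 × 2/18) = 0.784 to 12.4 × √((1 − 0.982²) × 2/18) = 0.781.

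**Small-sample cost.** The ratio treats the baseline slope as known. In an analysis of covariance at one visit with n per arm, estimating the slope inflates the variance by about 1 + 1/(2n − 4), which is 1 + 1/32 = 1.031 at n = 18. The ratios become 0.991 × 1.031 = 1.02 for T2-time, 0.974 × 1.031 = 1.00 for multifidus, 0.93 at r = 0.8, 0.77 at r = 0.5 and 0.67 at r = 0.3. A simulation agreed to within 0.002. There is thus no gain for the two outcomes with stated correlations, while most of the gain survives where r is modest.

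**Chance baseline imbalance.** A one-standard-error baseline difference in T2-time at 18 per arm is 12.4 × √(2/18) = 4.13 units. The difference in change retains (1 − 0.982) × 4.13 = 0.07 units, with opposite sign. A follow-up-only comparison would retain 0.982 × 4.13 = 4.06. At an assumed r = 0.5, a one-standard-error difference of 0.33 SD leaves 0.17 SD, half the standard error of the difference in change (0.33 SD).

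**Gender.** In one simulated balanced data set (20 per arm, three visits), the interaction estimate was 0.3751 and its standard error 0.6899, with and without a gender main effect. A constant gender effect cancels from a within-person contrast.

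**The case against.** The strongest reply is that the article is condensed and lists no covariates at all. A baseline covariate, a common baseline mean and gender are all compatible with its wording, and an analysis plan that is not shown may contain them. A group-by-time mixed model is also a valid and common analysis, and it matches the test for which the trial was sized. On the article's own correlations the loss is negligible.

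Most of this stands. It reduces the point to an efficiency improvement and rules out calling the plan wrong. What remains is that the article does fix the tested effect and does count baseline among its time-points. Read as written, that gives a difference in change. The 0.982 correlation for T2-time cannot be carried over to transversus abdominis thickness change, for which the article reports no reliability data.

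A reader might infer two stronger points. The first is that leaving gender out misstates the standard error. The article is silent on gender and does not exclude it, and a constant gender effect cancels in balanced data. Gender could matter if it modified response over time or if dropout unbalanced the data, but nothing in the article allows that to be sized. The second is that protection against chance imbalance in T2-time is lost. It is not, since 0.07 of 4.13 units remains.

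**Conclusion.** The point holds as a low-cost improvement. As written, the effect is a difference in change from baseline unless baseline means are constrained to be equal. It is unbiased under randomisation. Against baseline adjustment it gives up nothing of practical importance for T2-time (ratio 0.99) or multifidus area (0.97), and the cost of estimating the slope cancels even that at 18 per arm. For outcomes without a stated correlation, which include one of the two primary outcomes, the avoidable variance is 10% to 35% if r lies between 0.8 and 0.3, or about 7% to 33% after the small-sample cost.

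This rests on the assumed range of r, on equal variances across visits and on the article's wording being complete. It would be wrong to infer that the trial as a whole loses a quarter or a third of its sample, because that size belongs only to outcomes with low correlations, and those correlations are assumed.

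**What to change.** Replace the model sentence with wording such as: for each continuous outcome, a mixed model will be fitted to the 3- and 6-month values, with group, visit, group by visit, baseline value by visit and gender as fixed effects; the treatment effect is the adjusted between-arm difference at each visit. An equivalent choice is a constrained longitudinal model for all three time-points, with a common baseline mean across arms plus gender and gender by visit. Gender belongs in the statement because randomisation is stratified on it and the article does not say whether it enters.

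The cost is one sentence and a few degrees of freedom. Every variable is already collected. For T2-time the expected effect on precision is close to nil in either direction, so the reason for using one model throughout is consistency across outcomes. Trial status says recruitment was still under way at submission, so the model could be fixed before results are known.
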